## Background

Bacteremia is a common and serious problem affecting 15% of critically ill patients and resulting in a threefold higher mortality [1,2]. Among survivors, bacteremia is associated with a 2 to 7 day prolongation of intensive care unit (ICU) length of stay, a 2 to 3 week prolongation of hospital stay, and $25,000 to $40,000 in attributable excess costs [3,4].

The ICU is the location of greatest antimicrobial use in most hospitals; however, audits have revealed that 30 to 50% of antibiotic use in the ICU is unnecessary or inappropriate [5-7] and leads to avoidable drug side effects. Antibiotics are among the most common cause of serious adverse drug events [8], which occur in up to 5 to 10% of inpatient recipients [9]. Excessive durations of antibiotic therapy are the greatest contributor to inappropriate antibiotic use in acute care hospitals, long-term care facilities, and ambulatory care [6,10-12]. Discontinuing antibiotics after achieving clinical cure can potentially reduce the burden of adverse events (allergy and organ toxicity), *Clostridium difficile* infections, and additional costs and morbidity related to selection of antimicrobial resistant pathogens [13,14] Antibiotic resistance rates are rising among pathogens in ICUs [15] at the same time as the drug discovery pipeline is diminishing with very few new antimicrobial agents under development [16,17].

Meta-analysis of randomized controlled trials has demonstrated that shorter duration antibiotic therapy is as effective as longer duration antibiotic therapy for a range of mild to moderate infections [18]. Even in critically ill patients with ventilator-associated pneumonia, mortality rates and relapse rates were non-inferior among the 402 patients (of which only 7% were bacteremic) randomized to receive shorter (8 day) versus longer (15 day) courses of antibiotics [19]. However, similar high-grade evidence is lacking for the treatment of patients with bloodstream infections [1,20,21]. Specific guidelines for treatment durations exist for a variety of infections in ICU, including pneumonia [22,23], intra-abdominal infection [24], catheter-related bloodstream infection [25], pyelonephritis [26], and skin and soft tissue infection [27] but no guidelines exist for the optimal duration of treatment for bacteremic patients.

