### Primary and secondary outcome measures

The primary outcome for the main BALANCE trial is 90-day mortality and the primary outcome for the pilot trial is feasibility as defined by: (a) adherence to treatment duration protocol (proportion of treatment courses); and (b) rate of recruitment (patients per site, per month). We will consider the main trial to be feasible and worthy of embarking on a larger mortality-powered non-inferiority RCT if 90% of antibiotic treatment courses are within 7 ± 2 days in the shorter duration treatment arm or 14 ± 2 days in the longer duration treatment arm; and, if we achieve recruitment rates of at least 1 patient per 4 weeks, on average, per participating site. Secondary outcomes include ICU, hospital and 90-day mortality rates, relapse rates of bacteremia, antibiotic allergy and adverse events, rates of *Clostridium difficile* infection in hospital, rates of secondary infection or colonization with antimicrobial resistant organisms, ICU and hospital lengths of stay, mechanical ventilation duration, vasopressor duration in ICU and decline in procalcitonin levels.

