### Statistical analysis

#### Sample size

To estimate our expected adherence rate of 90% within a margin of error of ± 5% (that is, actual adherence 85 to 95%), with 95% confidence, we plan to enroll 115 patients. At our expected recruitment rate of 1 patient/site month across 15 sites, we will need approximately 10 to 24 months to recruit these 115 patients given variability in site trial start-up steps (REB approval, data sharing agreements and contracts). By the time we have recruited 115 patients, we will know with 95% confidence that this number of sites would be able to recruit 95 to 138 patients over the same time interval in a future trial; this data will then be used to estimate the number of centers needed for the main trial (see Additional file 1 for detailed sample size calculation).

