### Analysis of secondary outcomes

Mortality rates (at ICU discharge, hospital discharge and 90 days) will be measured as the proportion of patients alive or dead at these time points. We hypothesize that mortality rates will be non-inferior with 7 days of treatment; the main BALANCE trial will be powered to test this hypothesis. Continuous secondary outcomes, including lengths of stay in ICU and hospital, and durations of ventilation and vasopressor use, will be compared by Wilcoxon test. We will compare the ‘difference in differences’ between day 7 to 14 procalcitonin levels in the two treatment groups.

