### Frequency of analyses

The BALANCE Pilot Trial will be conducted and reported according to recommendations by the Consolidated Standards of Reporting Trials (CONSORT), including analyzing patients in the groups to which they were originally assigned (intention-to-treat) and explicit procedures for handling of any missing data [49].

Analyses will be conducted at the completion of this pilot, given that there is no role for early termination [50]. However, we will monitor recruitment and adherence rates weekly, and examine barriers as needed, working with participating centers to provide screening and consenting tips from prior CIHR-funded ICU trials [34]. Capturing a minimal dataset of patient, pathogen and bacteremia source characteristics among eligible nonenrolled patients will facilitate this, and comparisons with eligible patients will help to identify selection bias [49].

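### Stay, ventilation and vasopressor durations are compared by a Wilcoxon test on raw days with no rule for death, so an arm with more deaths can look better, modestly for ICU stay and more for hospital stay

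*Protocol article*

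**What the plan says.** Under Primary and secondary outcome measures, the protocol article lists among the secondary outcomes "ICU and hospital lengths of stay, mechanical ventilation duration, vasopressor duration in ICU". These are plain durations, not free days. Analysis of secondary outcomes fixes the test: continuous secondary outcomes, "including lengths of stay in ICU and hospital, and durations of ventilation and vasopressor use, will be compared by Wilcoxon test".

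Frequency of analyses commits to reporting by CONSORT, "including analyzing patients in the groups to which they were originally assigned (intention-to-treat"), so patients who die stay in the comparison. Death is handled only as an outcome of its own: mortality at ICU discharge, hospital discharge and 90 days "will be measured as the proportion of patients alive or dead at these time points". No section ranks death as worst, scores free days, treats death as a competing event or limits the durations to survivors.

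Three other statements bear on the size of the problem:
- Randomization and allocation concealment and Trial interventions withhold the assignment until the end of day 7 of adequate treatment.
- Frequency and duration of follow-up cites a retrospective study in which 27% had left ICU on or before day 7 and 4% had left hospital before day 7.
- Trial status says that, without substantive protocol changes, pilot patients will be carried into the main trial.

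**The concern.** A stay, a ventilation course or a vasopressor course ends either in recovery or in death. A rank test on raw days cannot tell these apart. A patient who dies in ICU on day 9 is ranked as having done better than one who leaves alive on day 12.

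The trial asks whether 7 days of treatment may be too short. If it were, and deaths followed, four secondary outcomes could credit the 7-day arm with shorter stays and less organ support. The section on the data safety and monitoring committee calls the pilot underpowered for mortality, so the mortality rows might not show a clear enough difference to warn the reader.

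**Working it through.** **What can be reproduced.** The article gives no expected mortality, stay or power for these comparisons, so there is no stated figure to reproduce. The Background says only that bacteremia is associated with higher mortality ("resulting in a threefold higher mortality"), with no rate. Everything below is illustration under stated assumptions, except the sample size ("we plan to enroll 115 patients"). Arms of 57 and 58 assume 1:1 allocation, which the article does not state.

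**Quantity computed.** The Wilcoxon statistic estimates P = U/(nA × nB), the chance that a random patient in arm A has a longer duration than one in arm B. Arm A has more deaths. It looks better when P < 0.5. With no effect this happens in 50% of trials, and a two-sided 5% test favours A in about 2.5%.

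**Step 1: early deaths, an upper illustration.** Assume identical underlying stays (lognormal, median 14 days, log-SD 0.8) and death times with median 5 days (log-SD 0.7) that truncate the stay.

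| Deaths A v B | Patients | Significant for A | Significant for B |
|---|---|---|---|
| 20% v 20% | 58 v 57 | 3.1% | 2.7% |
| 25% v 20% | 58 v 57 | 5.1% | 0.6% |
| 30% v 20% | 58 v 57 | 8.8% | 0.2% |
| 30% v 20% | 500 v 500 | 52% | 0% |
| 30% v 20%, deaths ranked worst | 58 v 57 | 0.2% | 15.3% |
| 30% v 20%, death times with median 25 days | 58 v 57 | 2.7% | 2.2% |

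The mechanism is real, ranking deaths worst removes it, and it nearly vanishes when deaths come late.

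**Step 2: fit to the design.** Assignment cannot cause deaths before day 7, so the excess belongs after it. Assume a 20% baseline risk in both arms, 10 points of excess after day 7 in arm A, log-SD 0.8, and median stays of 12 days (ICU) and 30 days (hospital). The medians can be set beside the article's own discharge figures:
- ICU: Φ((ln 7 − ln 12)/0.8) = Φ(−0.67) = 25%, against 27% in the retrospective study.
- Hospital: Φ((ln 7 − ln 30)/0.8) = Φ(−1.82) = 3.5%, against 4%.

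This is only a rough check, because the stay and treatment clocks need not start together.

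Results, as the share of trials in which the higher-mortality arm looks better:
- ICU stay, pilot size: about 56%.
- Hospital stay, pilot size: about 72%.
- Hospital stay, 500 per arm: about 95%.

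**Step 3: sensitivity to when the excess deaths occur.** The model of Step 2 was run again with two explicit timings. In both, the excess deaths fall on patients still in after day 7.

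| Timing of deaths | ICU, pilot | Hospital, pilot | Hospital, 500 per arm |
|---|---|---|---|
| Excess soon after day 7 (day 7 plus an exponential time, mean 10 days); baseline deaths with median 6 days | 60% | 70% | 94% |
| Deaths spread evenly (baseline over the stay, excess over the remainder after day 7) | 61% | 63% | 84% |

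With the first timing, hospital-stay tests at 500 per arm were significant for the higher-mortality arm in 35% of trials and for the other arm in 0%. With deaths ranked worst, the higher-mortality arm looked better in 17% of pilot-size trials, and significant results were 0.2% for it and 14.6% against it.

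If the excess deaths are instead given their own post-day-7 lengths of stay and do not truncate an ongoing stay, the ICU figure is 44% to 52%, which is chance. Ventilation and vasopressor durations were not simulated.

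**The case against.** The strongest reply is that the article never says in words that early deaths count as short durations. A Wilcoxon test is compatible with ranking deaths worst, and a full protocol or analysis plan, not shown, might say so. This stands as a caution. But the article names the scale, the test and the analysis set, and taken together these rank a death by its raw days.

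A reader might also infer that the analysis would probably reverse the result for ICU stay, picturing a death on day 5. The documents do not support that. Both arms are treated alike until the end of day 7, so deaths caused by the assignment come later. On later timings the ICU figure is close to chance, and 55% to 60% in the wrong direction is a modest bias.

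A third inference would be that the pilot's conclusions are at risk. They are not. The feasibility criteria are recruitment and adherence only, and the durations carry no decision rule. The stated aim of informing the main trial's design is attached to the subgroup analyses, not to these outcomes. Mortality is also reported beside the durations, so a careful reader would see both, though that does not correct the tests.

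Finally, replacing all four outcomes with free-day composites at chosen horizons would be partly a matter of preference, and raw stay does describe resource use. That is a fair reason for a smaller change.

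**Conclusion.** The concern holds in a limited form. As written, the comparison ranks a stay or course cut short by death as a good result and can favour the arm with more deaths. With 10 points of assumed excess mortality after day 7, the effect is small for ICU stay (about 56% of pilot-size trials in the wrong direction, and possibly none) and larger for hospital stay (about 72%, or 63% if the excess deaths are spread over the remaining stay). Hospital stay is more exposed because few patients have left hospital by day 7. At 500 per arm the hospital figure is 84% to 95%, so the rule matters most if pilot patients enter the main trial.

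The mortality rates, stay distributions and death times are all assumed. The direction for hospital stay is the firmer conclusion and the size is not. This is worth correcting as a secondary-outcome matter; it has no bearing on the feasibility decision.

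**What to change.** In Analysis of secondary outcomes, keep the Wilcoxon test and add one sentence: patients who die before ICU or hospital discharge, or before coming off ventilation or vasopressors, are ranked as the worst outcome for that duration. Free days with death scored 0 would be an acceptable equivalent. Report raw durations by survival status as description only, beside the mortality rates. A test restricted to survivors should not take its place, because it conditions on an event after randomization.

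The cost is small. Vital status at discharge and at 90 days is already collected, and treatment, data collection and sample size do not change. The rule should be settled before any comparison by arm, so that it carries unchanged into the main trial. The drawback is that the ranked outcome mixes death with duration and no longer describes resource use alone, which is why both displays are needed.

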### Trial interventions

We will randomize patients to receive a shorter duration of adequate antimicrobial therapy (7 days) versus a longer duration (14 days). Adequate antimicrobial treatment will be defined as a regimen with *in vitro* activity against the organism(s) responsible for the bloodstream infection; the duration of adequate treatment will be determined as the cumulative number of calendar days for which adequate treatment is delivered beyond the date of collection of the index blood culture specimen- the clock will start from initiation of the first adequate treatment dose after the blood culture has been drawn. The selection of specific antimicrobial agents, doses and route of delivery will initially be at the discretion of the treating clinical team. Most commonly the patient will already be receiving some empiric antibiotic treatment for suspected infection prior to the blood culture being documented as positive; the study protocol will not expose patients to potential antibiotic treatment delays. As soon as blood culture results are available (preliminary Gram staining), the research coordinator, in consultation with the site investigator and site infectious diseases co-investigator if necessary, will review the initial antibiotic choice to ensure adequate empiric coverage for the potential culprit organism(s). As blood culture results are finalized (speciation and sensitivity determination), they will re-review the antibiotic choice to ensure that the spectrum of activity is adequate. If the spectrum is inadequate, this will be communicated to the treating physicians. To avoid differentially influencing antibiotic choices and clinical decision-making, the randomization assignment will not be communicated to the study research coordinator, study critical care or infectious diseases investigators or clinicians until the end of day 7. The ICU research coordinator at each site will visit daily to ensure protocol adherence (antibiotics are stopped at the pre-specified date (end of the 7th or 14th day) and not earlier (Figure 1).

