### Blood samples for procalcitonin

Blood samples will be drawn on the randomization day and at days 7, 10 and 14 from the index blood culture collection to measure procalcitonin (PCT) levels. The PCT levels will be batched and measured at the end of the study for the sub-study assessing the association between PCT and clinical outcomes among patients receiving 7 versus 14 days of treatment. The results will not be made available to the treating team, because this could unduly influence clinical practice and protocol adherence, and is ethical because none of the participating sites are currently using PCT as part of routine clinical practice. Following study completion, we will compare PCT area-under-the-curve (AUC) and day 14 PCT levels among patients receiving 7 versus 14 days of antibiotics. We will also confirm whether 7 days of antibiotics is non-inferior to 14 days of antibiotics for bacteremia, in subgroups with both normal and abnormal PCT levels on day 7.

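### Neither procalcitonin comparison adjusts for the day-7 level; an ANCOVA of day-14 on day-7 would be an optional gain in precision on a valid analysis

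*Protocol article*

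**What the plan says.** Three sections of the protocol article describe the procalcitonin comparison.

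- Analysis of secondary outcomes plans a difference-in-differences "between day 7 to 14 procalcitonin levels in the two treatment groups". No scale is named and no covariate is mentioned.
- Blood samples for procalcitonin: "we will compare PCT area-under-the-curve (AUC) and day 14 PCT levels among patients receiving 7 versus 14 days of antibiotics". Again, no scale or adjustment is stated.
- Primary and secondary outcome measures ends its list with "vasopressor duration in ICU and decline in procalcitonin levels".

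None of the three is designated as the main procalcitonin analysis.

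On timing, Blood samples for procalcitonin states: "Blood samples will be drawn on the randomization day and at days 7, 10 and 14 from the index blood culture collection". Under Trial interventions, the assignment is withheld from coordinators, investigators and clinicians "until the end of day 7". The assays are batched and run after the study ends.

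**The concern.** A between-arm comparison of day 7-to-14 changes subtracts the whole day-7 value from the day-14 value, which fixes the day-7 coefficient at 1. A chance imbalance at day 7 is then over-corrected whenever the true regression slope is below 1. An unadjusted comparison of day-14 levels errs the other way, because it fixes the coefficient at 0. ANCOVA estimates the coefficient from the data and, in large samples, is never less precise than either.

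What is at stake is the width of the interval for one secondary comparison in a trial of 115 patients. Validity is not in question.

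**Working it through.** **Inputs from the article.** The total is 115 patients (Sample size). Procalcitonin is sampled at days 7 and 14 from the index culture. Assignment is concealed to the end of day 7 of adequate treatment. The article gives no SD, correlation, target difference or power for procalcitonin, so there is no procalcitonin figure to reproduce.

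**Is day 7 a legitimate covariate?** The treatment clock starts with the first adequate dose after the culture is drawn. Day 7 from culture is therefore normally no later than day 7 of adequate treatment, and until then both arms are managed alike without knowledge of assignment. The day-7 value normally precedes divergence of the arms.

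**Assumptions.** rho is taken from 0.2 to 0.9. The day-14 SD is k times the day-7 SD, with k = 1 first and then 0.8 and 1.2.

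**Variances per patient, in units of the day-7 variance.**
- Change score: 1 + k² − 2k·rho
- Day-14 level alone: k²
- ANCOVA: k²(1 − rho²)

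The change-score variance exceeds the ANCOVA variance by (1 − k·rho)², which is never negative. The direction therefore does not depend on the assumed values. Only the size does.

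**Equal SDs (k = 1).** The ratio of ANCOVA to change-score variance is (1 − rho²)/[2(1 − rho)] = (1 + rho)/2, so the information lost by the change score is (1 − rho)/2. The unadjusted day-14 level loses rho².

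| rho | Lost by change score | Lost by day-14 level alone |
|---|---|---|
| 0.2 | 40% | 4% |
| 0.4 | 30% | 16% |
| 0.5 | 25% | 25% |
| 0.7 | 15% | 49% |
| 0.9 | 5% | 81% |

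**Unequal SDs, change score against ANCOVA.**
- k = 0.8, rho 0.4: 0.64 × 0.84 / (1.64 − 0.64) = 0.538, a loss of 46%.
- k = 0.8, rho 0.7: 0.64 × 0.51 / (1.64 − 1.12) = 0.628, a loss of 37%.
- k = 1.2, rho 0.4: 1.44 × 0.84 / (2.44 − 0.96) = 0.817, a loss of 18%.
- k = 1.2, rho 0.7: 1.44 × 0.51 / (2.44 − 1.68) = 0.966, a loss of 3%.

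**In patients (k = 1, all 115 with both samples).** At rho 0.4 the change score is worth 115 × 0.70 = 80.5, or about 81 patients analysed by ANCOVA. At rho 0.7 it is worth 115 × 0.85 = 97.75, or about 98.

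**In power (k = 1, two-sided 5%).** Take an effect that ANCOVA detects with 80% power, so its standardised size is 1.96 + 0.84 = 2.80.
- Change score: 2.80 × √0.70 − 1.96 = 0.38, or 65% power at rho 0.4; 2.80 × √0.85 − 1.96 = 0.62, or 73% at rho 0.7.
- Unadjusted day-14 level: 2.80 × √0.84 − 1.96 = 0.61, or 73% at rho 0.4; 2.80 × √0.51 − 1.96 = 0.04, or 52% at rho 0.7.

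**Validity.** In lognormal simulations (58 per arm, log SD 1.0 and 1.5, rho 0.4 and 0.7, 3,000 runs per setting) with no true difference, the rejection rate was 3% to 6% for every method, including change on the untransformed scale.

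**The case against.** The planned analysis is a legitimate one. A change-score comparison between randomised arms is unbiased, and the simulations show no inflated error rate. The article claims no power for procalcitonin, and its sample size rests on the adherence estimate. This stands: the point concerns efficiency alone.

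The change score is also not the only plan, since the sub-study section compares day-14 levels and area under the curve. That is correct, but the day-14 comparison has no stated adjustment either, and above rho 0.5 with equal SDs it loses more information than the change score does.

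Scale and covariates are matters that a condensed article may leave to a fuller document. That stands for the scale. The difference-in-differences, however, is stated outright, and an analysis plan written from that sentence would inherit it.

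A reader might go further and infer that the result is open to distortion by skewed values, or that power would collapse on the untransformed scale. The article does not support this. It names no scale, does not exclude logs and says nothing about the distribution of procalcitonin. It also says: "Continuous secondary outcomes, including lengths of stay in ICU and hospital, and durations of ventilation and vasopressor use, will be compared by Wilcoxon test". The listed examples omit procalcitonin, but the sentence may be meant to cover it.

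A reader might also take a loss of 15% to 30% as established. That range is only what equal SDs and rho from 0.7 down to 0.4 would give, and the article states neither.

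**Conclusion.** The point holds as an optional improvement. Neither stated procalcitonin comparison adjusts for a day-7 level that is already collected and normally precedes divergence of the arms. The planned change comparison is valid but, unless the regression slope of day 14 on day 7 equals 1, less precise than ANCOVA.

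The size is an assumption throughout. With equal SDs the loss runs from 5% (rho 0.9) to 40% (rho 0.2). For rho between 0.4 and 0.7 it is about 3% to 18% if the day-14 SD is 1.2 times the day-7 SD, and 37% to 46% if it is 0.8 times. The direction is secure.

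The consequence is limited to the precision of a secondary outcome in a pilot judged on recruitment and adherence.

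**What to change.** In Analysis of secondary outcomes, replace the procalcitonin sentence with: the main procalcitonin comparison is an ANCOVA of log day-14 level on treatment arm and log day-7 level, reported as a ratio of geometric means with 95% CI. State in the same place that the day 7-to-14 change and the area under the curve are supportive. Bring Blood samples for procalcitonin and Primary and secondary outcome measures into line, so that all three sections name the same main analysis.

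Adding site as a covariate is optional. Its small downside is the degrees of freedom used: with up to 15 sites, 15 − 1 = 14 as fixed effects. The precision figures above are for a model without site.

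The cost is wording only, with no further samples or patients. Because the assays are run after the study ends, the choice can be fixed before any procalcitonin result exists.
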